### Exclusion criteria

Data from births will not be included in collection and analysis if any of the following apply:An operative birth instrument was only applied during (and not before) a caesarean section (i.e. use of Wrigley’s forceps at caesarean)The woman had a multiple pregnancy (twins or higher)If the woman is < 18 years old at the time of birthIf the woman is a prisoner

### Time period of outcomes studied

12 months. Of this, data will be collected for three to 6 months prior to each unit of trainees attending OVB simulation training and four to 6 months after. This equates to 12 months of outcomes studied per site, due to variable data collection lengths of different sites. The time period of the training intervention will be two to 3 months, depending on the ability of participating units to implement training at higher frequencies to train all of their individual doctors.

Data will not be collected during the training intervention period. Doctors within units will be trained at different rates within the training periods, and so no comparison can be made between training periods between units as at any given time different proportions of doctors will have been exposed to training.

### Primary outcome measure

The primary outcome measure will be failed operative vaginal birth with first chosen instrument. This has been chosen as failure with the first instrument will lead to either use of a second instrument or reversion to caesareans section – both of which have been demonstrated to be independently associated with poorer outcomes than success with the first instrument [3, 10]. Moreover, this is the chosen primary outcome of the most recent Cochrane review of the subject [11].

### Secondary outcome measures

The following secondary maternal outcomes measures will be collected; use of second instrument to achieve OVB, caesarean section, episiotomy, perineal trauma (1st, 2nd, 3rd, 4th degree tear), cervical tear requiring suturing, general anaesthesia and estimated blood loss (EBL). The following secondary neonatal outcomes will be collected; Apgar score at 1, 5, 10 min, Umbilical artery pH, shoulder dystocia, admission to Neonatal Intensive Care Unit (NICU), death within 28 days of birth.

### Clinical variable characteristics

The following clinical variable characteristics will be collected and used for adjusting and comparing secondary clinical outcomes; maternal age (years), body mass index (BMI) at booking, parity, history of previous caesarean or vaginal birth, length of gestation (completed weeks), duration of first and second stage (minutes), indication for assisted vaginal birth (presumed fetal compromise, delay in 2nd stage, maternal exhaustion, other), rotation required as part of OVB (Yes/No), analgesia (epidural block, spinal block, general anaesthesia, pudendal block, perineal infiltration, none), baby birth weight (g), grade of operator (Speciality Trainee (years of residency in O&G) (ST) 1–2, ST 3–5, ST 6–7, Consultant), grade of supervisor (if applicable, ST 3–5, ST 6–7, Consultant).

### Process measures

The following will be recorded as process measures; number and proportion (%) of trainees exposed to intervention per site during training period, number and seniority of local facilitators of intervention.

### Frequency of primary outcome measure and expected measure of effect

The primary outcome is failed OVB. Depending on the type of OVB, rates of failure in reported studies vary between 5.8% (rotational forceps) [12, 13], 9.3% (non-rotational forceps), 14.1% (all types of ventouse) and 24.4% (hand-held ventouse) [11].

We propose to take 80% as an estimated real-world success rate (this is lower than that reported in other studies, as OVBs reported in studies will be subject to the Hawthorne effect. We also seek to reflect the mix of types of OVB performed).

### Sample size

We have generated the following study power calculations scenarios using sample size formulae for stepped-wedge design proposed by Hussey et al. [14] and implemented in Stata by Hemming et al. [12]. We have used a two-sided alpha of 0.05 and assumed an inter-cluster co-efficient (ICC) of 0.1.

### Conservative estimate

Assuming 4 units, each exposed to the intervention at a different step (Table 2), i.e. one unit per step, each step of 3 months length, at least one observation period prior to the implementation of the intervention and one period after its implementation, and no data collected during the intervention implementation (washout-period) and 200 births per unit per period/step, the study will be able to detect a change from 20 to 10% in the proportion of failed OVB with a 76% power.

**Table 2 Tab2:** Stepped-wedge interrupted time series design of STROBE study

	Step 0	Step 1	Step 2	Step 3	Step 4	Step 5
Unit 1	Pre-training data collection period	Intervention implemented, no data collected	Post-training data collection period	Post-training data collection period	Post-training data collection period	Post-training data collection period
Unit 2	Pre-training data collection period	Pre-training data collection period	Intervention implemented, no data collected	Post-training data collection period	Post-training data collection period	Post-training data collection period
Unit 3	Pre-training data collection period	Pre-training data collection period	Pre-training data collection period	Intervention implemented, no data collected	Post-training data collection period	Post-training data collection period
Unit 4	Pre-training data collection period	Pre-training data collection period	Pre-training data collection period	Pre-training data collection period	Intervention implemented, no data collected	Post-training data collection period

### Optimistic estimate

Using the same set of hypotheses but assuming 266 births per unit per period, the same change would be detected with a power of 89%.

Based on the delivery figures for the 4 units for 2016–2017, around 250 (eligible) deliveries are expected per three-month periods, suggesting that for a 12 month period (defined as per funding constraint and to limit contamination due to trainees rotating between hospitals), we expect the power to be between 76 and 89% to detect a 50% reduction in failed OVB from 20 to 10%.

### Data collection

Study data will take the form of electronic and paper-based clinical patient notes at each study site. Data will be extracted and uploaded following collation onto a study-specific iteration of a secure electronic database hosted by the University of Bristol (*REDcap*) using password-protected NHS computers.

All data held on secure computing networks (both NHS and University of Bristol) will be protected by using a combination of passwords and file permissions.

All files, paper and electronic data will be transferred to secure archiving no more than 3 years after the end of the study. Data will be stored for 5 years after the study is complete, in line with the MRC Guidance on Personal Information in Medical Research [13]. Data procedures will be in keeping with the stipulations in the Data Protection Act 2000.

### Data analysis

#### Participation, loss to follow-up and withdrawal

While the current study design is not a formal stepped-wedge study design, and has no randomisation component, its analysis and reporting will respect the principles of the CONSORT guideline [15] and available guidelines for stepped-wedge design at the time of analysis. Unit recruitment, in-house trainers’ participation in training and in-house training implementation will be documented as frequency and proportions.

Loss to follow-up will only occur if a maternity unit is closed. To our knowledge, no unit closures or merging are planned for the duration of the project.

#### Baseline and intervention description

The total and unit-specific number of births (count), OVB (count), failed attempted OVB (count) and rate of failed attempted OVB (%) will be tabulated by step/period (zero to five).

The frequency and proportion of staff trained and number of training sessions delivered by in-house trainers will also be reported for each of the 4 units. Proportions, means with standard deviation or median with inter-quartile range will be reported as appropriate to describe the maternal and neonatal outcomes.

#### Main analysis

The outcome for the main analysis is the rate of successful attempted OVB in term infants, dichotomised into successful or failed. This dichotomous outcome measured for each birth will be analysed with a modified Poisson regression (with robust estimation of the variance) [16]. All models will be adjusted for hospital units as fixed to account for clustering at maternity unit level, i.e. correlation between births occurring in the same maternity unit. A formal mixed or marginal regression model cannot be considered due to the reduced number of hospital units involved in this study (n = four).

In the main analysis, we will assess the intervention effect (control periods vs. post-intervention periods) and include an adjustment for the time period (period zero to five) to account for any underlying time trend susceptible to confound the assessment of the main effect [17, 18]. We will either model the time periods with categorical fixed effect variables (with dummy indicators for each period) or as a continuous factor with appropriate polynomial function of time if required. Statistics such as the Aikeke information criterion will be used to select the best modelling for time.

The interaction between time and the main intervention effect will then be modelled to investigate the timing and duration of the intervention effect. The study is not powered for such interaction and this last model should be considered as exploratory.

We will use the Log-likelihood ratio or Wald test and *p*-value of 0.05 to assess the strength of the association, assuming that any p-value equal or below 0.05 (two-sided) will show evidence of an association between the intervention and outcome.

No interim analysis is planned.

The model will then be adjusted for patient, delivery or hospital characteristics susceptible to influence the primary or secondary outcome such maternal BMI, length of second stage of labour and fetal weight. These analyses will be conducted on an intention-to-treat principle, i.e. a unit will be considered as exposed to the intervention 3 months after the initial planed date of intervention implementation.

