**Methods:**

The STROBE study is a quasi-experimental before-after interrupted time-series study of the effect of simulation training in operative vaginal birth for obstetricians on clinical outcomes of women and babies following operative vaginal birth. Similar to a stepped-wedge design, the intervention will be gradually implemented in all participating units but at different time periods. The primary outcome is failed operative vaginal birth with the first intended instrument. Secondary maternal outcomes are; use of second instrument to achieve operative vaginal birth, caesarean section, episiotomy, perineal trauma (1st, 2nd, 3rd, 4th degree tear), cervical tear requiring suturing, general anaesthesia and estimated blood loss. Secondary neonatal outcomes are; Apgar score at one, five, and ten minutes, Umbilical artery pH, shoulder dystocia, admission to Neonatal Intensive Care Unit and death within 28 days of birth. The analysis will be intention-to-treat (per unit) on the primary and secondary outcomes. The STROBE study received approval from the Health Research Authority and is sponsored by North Bristol NHS Trust. Results will be published in an open-access peer-reviewed medical journal within one year of completion of data gathering.

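### The main-analysis sentence adds an undefined restriction to term infants that the eligibility criteria do not contain, and leaves out the first-instrument condition of the declared primary outcome.

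*Protocol article*

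**What the plan says.** The outcome is declared in full twice. The Abstract says "The primary outcome is failed operative vaginal birth with the first intended instrument", and Primary outcome measure says "The primary outcome measure will be failed operative vaginal birth with first chosen instrument". The latter section gives the reason: "failure with the first instrument will lead to either use of a second instrument or reversion to caesareans section", both of which it links to poorer outcomes.

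Main analysis then states: "The outcome for the main analysis is the rate of successful attempted OVB in term infants, dichotomised into successful or failed". It specifies a modified Poisson regression, which yields a risk ratio.

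The population is described in three places. Participants covers all attempted operative vaginal births (OVB) in the four units. Inclusion criteria ask for a vaginal birth at a study site in the study period and for forceps or vacuum applied to the fetal head. Exclusion criteria list an instrument used only during caesarean, multiple pregnancy, age under 18, and prisoners. None mentions gestation. Clinical variable characteristics lists "length of gestation (completed weeks") among the variables for adjustment and comparison.

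Elsewhere the outcome is shortened. The effect-size section says "The primary outcome is failed OVB", and the descriptive tables will show "failed attempted OVB (count) and rate of failed attempted OVB". The sample-size text and the missing-data rules under Sensitivity analyses also omit the first instrument.

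**The concern.** An analyst who follows the Main analysis sentence departs from the rest of the protocol in one definite way and one possible way.

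- **Population.** Preterm births that meet every eligibility criterion would be dropped, and the analyst would have to choose the gestational cut-off.
- **Event.** Secondary outcome measures lists "use of second instrument to achieve OVB, caesarean section, episiotomy", so the article's own language treats a second-instrument delivery as an OVB that was achieved. Under the literal Main analysis wording that birth is a success. Under the declared primary outcome it is a failure.

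The headline result is at stake: the text permits more than one primary analysis and does not choose between them. The study is not randomised, was registered retrospectively, and was already collecting data in July 2018. A single event and a single population, fixed before analysis, are therefore an important safeguard.

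**Working it through.** **1. Population, side by side.**

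| Section | Gestational limit |
|---|---|
| Participants | none |
| Inclusion criteria | none |
| Exclusion criteria | none |
| Clinical variable characteristics | gestation recorded as a covariate |
| Main analysis | term infants, undefined |

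Main analysis stands alone and conflicts with the others.

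**2. Event, by route of birth after the first instrument is applied.**

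| Route | Declared primary outcome | Main analysis, read literally |
|---|---|---|
| Completed with first instrument | not failed | successful |
| Completed with second instrument | failed | successful |
| Caesarean | failed | failed |

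The two definitions differ only in the second row.

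**3. Coding.** The planned effect is 20% to 10% failed, with baseline success taken as 80%. As failure the risk ratio is 0.10/0.20 = 0.50. As success it is 0.90/0.80 = 1.125. The absolute difference is 10 percentage points either way, and the power formula below gives the same power for both codings.

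**4. The plan's own power figure.** Inputs from Sample size and Table 2: 4 units, 6 periods, implementation cells empty, ICC 0.1, two-sided alpha 0.05, 200 or 266 births per unit-period, 20% to 10%. Method: Hussey-Hughes generalised least squares with a random unit intercept and fixed period effects; power = Φ(|difference|/SE − 1.96). The binary variance is the mean of the two binomial variances, and the ICC is taken on total variance.

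This gives 97% at 200 births and 99% at 266, against the stated 76% and 89%. Other variance and ICC conventions on Table 2 gave 91% to 97% at 200. No variant tried gave both stated values within 2 points. The software settings are not reported, so this does not prove an error, and the point made here does not depend on it.

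**5. Effect of losing the first-instrument condition.** Let s be the share of first-instrument failures completed with a second instrument, equal before and after training. The article gives no value, so s is an assumption. Failure under the literal reading is 0.20(1 − s) before and 0.10(1 − s) after. On Table 2 with 200 births per cell, SE = 0.0722 × σ, where σ² is the mean binomial variance.

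| s | Failure, before to after | σ² | SE | Power, 200 | Power, 266 |
|---|---|---|---|---|---|
| 0 | 20% to 10% | 0.1250 | 0.0255 | 97% | 99% |
| 0.25 | 15% to 7.5% | 0.0984 | 0.0227 | 91% | 97% |
| 0.50 | 10% to 5% | 0.0688 | 0.0189 | 75% | 86% |
| 0.75 | 5% to 2.5% | 0.0359 | 0.0137 | 45% | 56% |

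Example, s = 0.50: 0.05/0.0189 − 1.96 = 0.69, and Φ(0.69) = 75%. With the baseline variance instead, power at 200 births is 93% for s = 0 and 64% for s = 0.50.

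**6. Effect of the term restriction.** If 90% to 97% of eligible births are term (assumption), 3000 × 0.03 = 90 to 3000 × 0.10 = 300 births are dropped. Power at 200 births per cell is then 96% to 97%, against 97%.

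**The case against.** The strongest reply is that Main analysis uses shorthand. The outcome is defined in full in two places and then abbreviated in the effect-size section, the sample-size text, the descriptive tables and the missing-data rules. The effect-size section explicitly calls the short form the primary outcome. Reading Main analysis the same way is at least as natural as reading it as a new endpoint. This stands. A reader might infer that the primary endpoint was switched, or left open so that it could be chosen after the data are seen; the article supports neither. It also does not say that training acts mainly on second-instrument use.

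A second reply is that success and failure are complements of one variable. This also stands: the sentence names both levels, does not say which is modelled, and the protocol itself sets its baseline as a success rate. A reader might call these different outcomes, but only the reported ratio differs.

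A third reply is that the power losses are hypothetical. They need the literal reading here, the first-instrument reading of the sample-size text, and an assumed share. They also start from 97%, which is not the protocol's 76%. They show sensitivity and do not predict a loss.

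None of these replies answers the term restriction, which no other section uses or explains.

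**Conclusion.** The term restriction is a plain contradiction with the study population and eligibility criteria, and it is undefined. Its harm is that the analysed population is unclear; the loss of power is about one percentage point or less if at least 90% of eligible births are term.

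The missing first-instrument condition is an ambiguity that needs removing, not an established change of endpoint. If the sentence were followed literally, power on Table 2 at 200 births per cell would lie anywhere from about 97% down to 45% as the second-instrument share runs from 0 to 75%. Those figures rest on the assumed share, the chosen variance convention and a formula that did not reproduce the stated power. Success or failure coding is a reporting point only.

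Because the sentence governs the primary analysis, it should be corrected before the data are analysed.

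**What to change.** 1. State in Main analysis that the modelled event is failure with the first chosen instrument: the birth was not completed with that instrument, including use of a second instrument or caesarean. Report a risk ratio for failure, which matches the effect used for sample size.
2. State the analysis population as all births with an instrument applied to the fetal head before any caesarean and with none of the listed exclusions.
3. Reconcile the term restriction with eligibility. Either delete it, make term births a sensitivity analysis with a stated gestational definition, or add a defined gestational limit to the eligibility criteria. The article does not show which was intended.
4. Reword the inclusion criterion that requires a vaginal birth. Since all inclusion criteria must apply, read literally it removes caesareans after an attempted OVB, which are primary-outcome events. Simply pointing the main analysis at the present criteria would carry that problem over.

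The cost is a few sentences of rewording. The instrument sequence, caesarean and gestation are already to be collected, so no new data are needed.

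### The planned interaction with calendar period cannot show how long the training effect lasts, and the single constant effect in the main model can be distorted if the effect changes after training

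*Protocol article*

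**What the plan says.** All statements are in the protocol article.

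- **Main effect.** Under Main analysis, "we will assess the intervention effect (control periods vs. post-intervention periods") is the primary contrast: one on/off term in a modified Poisson model with fixed unit effects.
- **Time.** The model will "include an adjustment for the time period (period zero to five"), either "with dummy indicators for each period" or as a polynomial, chosen by an information criterion.
- **Duration.** The same section continues: "The interaction between time and the main intervention effect will then be modelled to investigate the timing and duration of the intervention effect". It calls this model exploratory and says that the study is not powered for it.
- **Layout.** Under Conservative estimate, the four units are "each exposed to the intervention at a different step (Table 2), i.e. one unit per step, each step of 3 months length", with "no data collected during the intervention implementation (washout-period"). Table 2 shows the resulting cells over steps 0 to 5.
- **Data window.** Time period of outcomes studied gives a shorter window than Table 2: three to six months before training and four to six months after.

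**The concern.** How long a training effect lasts is a question about time since training. In step 5 of Table 2, Unit 1 is in its fourth quarter after training and Unit 4 in its first. An effect for that calendar step pools the two and describes neither. The late steps also have no untrained comparator.

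The main model has a related exposure. Units that are already trained help to estimate the period effects. If their effect fades, the model reads part of the fade as a general worsening over time and credits the intervention for offsetting it. If the effect builds, the reverse happens.

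A changing effect is plausible on the protocol's own terms. The intervention is a one-day course, the 12-month period was set partly "to limit contamination due to trainees rotating between hospitals", and the plan itself asks about timing and duration. At stake are the duration question and the meaning of the primary ratio, on which the Discussion would judge a nationwide programme.

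**Working it through.** **Inputs.** Cells of Table 2: 20 unit-steps with data, 10 of them trained. Baseline failure 20% and target 10% (ratio 0.50), from Sample size. About 250 births per unit-quarter, from Optimistic estimate. The fade and build paths are assumptions, because the protocol gives none.

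**The plan's own figures.** With a constant ratio of 0.50 the main model returns exactly 0.50, so it is sound when the effect is steady. The stated power of 76% at 200 births per cell was not reproduced on Table 2 as printed (about 91% to 99.6%, by choice of variance). That is a separate matter, and nothing below depends on it.

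**Step 1: can the interaction be estimated?** Unit effects (4), period dummies (5) and intervention effects at steps 2, 3, 4 and 5 (4) make 13 columns. At step 4, Units 1 to 3 are trained and Unit 4 is in its training step with no data. At step 5 all four are trained. In each of these steps the interaction column equals the period dummy, so the rank is 13 − 2 = 11. Only steps 2 and 3 are estimable. Even there the values can mislead: a fade of 0.50, 0.60, 0.70, 0.80 by quarter since training gives 0.42 at step 2 and 0.48 at step 3, both below every true ratio.

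**Step 2: what does the constant effect average?** On the log scale, by unweighted least squares with unit and period dummies on Table 2, the weights on the first to fourth quarter since training (b0 to b3) are +1.25, +0.25, −0.25, −0.25:

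estimate = b0 + 0.25[(b0 − b2) + (b1 − b3)]

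A steady rise or fall in the effect therefore pushes the estimate past b0, away from the later effects. Hand check for 0.50, 0.65, 0.80, 1.00: 1.25(−0.693) + 0.25(−0.431) − 0.25(−0.223) − 0.25(0) = −0.918, a ratio of 0.40. The Poisson fit weights cells differently and gives 0.43.

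**Step 3: Poisson limits by layout** (period dummies, expected values)

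| Layout | Fade 0.50, 0.65, 0.80, 1.00 | Fade 0.50, 0.55, 0.60, 0.65 | Build 0.80, 0.70, 0.60, 0.50 |
|---|---|---|---|
| Table 2 | 0.43 | 0.47 | 0.90 |
| Two quarters each side | 0.43 | 0.47 | 0.89 |
| All pre-training cells, two quarters after | 0.505 | 0.502 | 0.809 |
| Table 2 plus four earlier control quarters | 0.49 | 0.50 | 0.82 |
| Table 2, Unit 4 never trained | 0.585 | 0.53 | 0.754 |

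Where only two quarters follow training, only the first two values of each path apply. The geometric means over the 10 trained cells of Table 2 (4, 3, 2 and 1 cells in the first to fourth quarter) are 0.64, 0.55 and 0.69. On Table 2, linear time gives 0.44, 0.48 and 0.89, and quadratic time 0.43, 0.47 and 0.90, so choosing the time coding by information criterion does not remove the distortion.

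**Step 4: the alternative.** Four indicators for quarters since training, in place of the interaction, give 4 + 5 + 4 = 13 columns of rank 13, and return the true values in the large-sample limit. Standard errors of the log ratio at 250 births per cell and a ratio of 0.50 are 0.18, 0.23, 0.30 and 0.38, against 0.17 for the constant effect. With two quarters each side there are two indicators (4 + 5 + 2 = 11 columns, rank 11), with standard errors 0.27 and 0.37.

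**The case against.** The strongest objections, and what stands of each:

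- **The paths are invented, and the distortion depends on the layout.** This stands. A reader might infer from the Table 2 figures that the primary ratio must lie outside the true effects. The documents do not support that. The result is in range, or at most slightly outside, with all pre-training cells and two quarters of follow-up, with the longer control period floated under Sensitivity analyses, or with the never-trained control site foreseen under Study design. The second is tentative and the third a contingency, so neither secures the plan. With two quarters each side, which fits the stated data window, the distortion is as large as on Table 2.
- **Polynomial time makes the late effects computable.** This is true, so it would be too strong to say that the interaction can never be estimated after step 3. What it yields there is an untrained trend carried into steps with no untrained data.
- **Time could mean time since training, and such coding can be left to an analysis plan.** The sentence does say only time. But the section defines one time variable, calendar period, and ties the interaction to a stated aim. That makes it a stated analysis that does not fit its aim, not an omitted detail.
- **The interaction is labelled exploratory.** This limits the weight of that part. The label does not cover the constant-effect main model.

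**Conclusion.** The point holds as a matter of analysis wording. As written, the interaction cannot describe duration: it uses the wrong time scale, and in Table 2 it has no untrained comparator at steps 4 and 5. That part follows from the layout and needs no assumption about the effect, except that a unit which never trains would restore estimability.

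The point about the primary ratio is conditional. If the effect changes with time since training, the ratio can be distorted: 0.43 for the steep assumed fade and 0.90 for the assumed build on Table 2, with little or no out-of-range error under some other layouts. A reader might conclude that the primary model is invalid or that the training effect will fade. Neither follows. The model is exact for a steady effect, and the protocol gives no decay or learning curve.

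**What to change.** 1. Keep the constant-effect primary model, and state that its ratio assumes a steady effect after training.
2. Replace the exploratory calendar interaction with indicators for quarters since the end of the unit's training window, keeping unit and period effects. Count from the planned date in the intention-to-treat analysis and from the actual date in the as-implemented analysis.
3. Report the ratio by quarter since training. Pre-specify the average of these, with its weights, as a sensitivity estimate beside the primary ratio.
4. State how many post-training quarters exist. Table 2 allows four, but a follow-up of four to six months allows only two.

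The cost is wording: only training dates and birth dates are needed. The quarterly estimates are less precise. At standard errors of 0.18 to 0.38, the 95% limits lie a factor of exp(1.96 × 0.18) = 1.42 to exp(1.96 × 0.38) = 2.1 either side, which is why they should stay exploratory. There is also a limit. If every unit had only one pre-training quarter, calendar period would equal a unit constant plus a function of time since training, and the indicators could not all be estimated. At least some units need a second pre-training quarter, as Table 2 gives Units 2 to 4.

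### The main analysis permits a likelihood-ratio test, or a Wald test with no stated variance, for a modified Poisson model that is valid only with the robust variance; if success is the modelled event, the likelihood-ratio test loses most of its power

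*Protocol article*

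**What the plan says.** All of the operative text is in the Main analysis section of the protocol article.

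- **Model.** The per-birth dichotomous outcome is "analysed with a modified Poisson regression (with robust estimation of the variance", with hospital unit as a fixed effect and an adjustment for period (zero to five).
- **Test.** "We will use the Log-likelihood ratio or Wald test", at two-sided 0.05. Neither test is preferred, and the Wald test is not tied to a particular variance.
- **Time.** Periods enter either as categories or as a polynomial, and "Statistics such as the Aikeke information criterion will be used to select the best modelling for time".
- **Event.** "The outcome for the main analysis is the rate of successful attempted OVB in term infants, dichotomised into successful or failed".

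The Primary outcome measure section words the event the other way: "The primary outcome measure will be failed operative vaginal birth with first chosen instrument". The planning rate is given as success ("We propose to take 80% as an estimated real-world success rate"), while the Sample size scenarios are given as failure, 20% falling to 10%.

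**The concern.** Modified Poisson regression applies a Poisson likelihood, whose variance equals the mean p, to a binary outcome whose variance is p(1−p). The likelihood is knowingly wrong, and inference is rescued by replacing the model-based variance with the sandwich estimator. A likelihood-ratio statistic comes straight from the wrong likelihood and never uses the sandwich. So the section requires a robust variance and, a few sentences later, permits a test that discards it. A Wald test with the model-based variance has the same defect.

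The Poisson variance is too large by a factor of 1/(1−p). That is small when the event is uncommon and large when it is common, so the choice between failure (10-20%) and success (80-90%) as the event decides whether this matters. At stake is a false negative on the primary hypothesis. The Discussion says that an equivocal or negative result should lead to the training being re-evaluated and redesigned. Leaving the test open also allows two very different p-values from the same fitted model.

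**Working it through.** **Inputs from the protocol article.** Table 2 layout: 4 units, 6 periods, one implementation cell per unit without data, so 4 × 6 − 4 = 20 data cells. 200 births per cell (conservative) or 266 (optimistic). Failure 20% to 10%, that is, success 80% to 90%. Two-sided alpha 0.05. Unit and period fixed effects. The ICC of 0.1 does not enter the comparison, because unit fixed effects absorb between-unit differences.

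**The plan's own figures.** The stated power is 76% at 200 births and 89% at 266. The stepped-wedge formula that the protocol cites, applied to Table 2 with ICC 0.1, gave 91-99% and 97-99.9%, depending on the variance convention, so the stated figures were not reproduced. A continuity-corrected comparison of two proportions gives 76.0% (200 per group) and 87.7% (266 per group), but that is not the stated method. The mismatch does not affect the comparison of tests below.

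**Step 1, scale of the error.** 1/(1−p):
- success: 1/0.2 = 5 at 80%, 1/0.1 = 10 at 90%;
- failure: 1/0.8 = 1.25 at 20%, 1/0.9 = 1.11 at 10%.

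**Step 2, type I error.** Under the null the likelihood-ratio statistic behaves like (1−p) × chi-square(1), so the true rejection rate is P(chi-square(1) > 3.841/(1−p)).
- Success at 80%: 3.841/0.2 = 19.2, rate about 0.00001 (simulated 0 to 0.0003).
- Failure at 20%: 3.841/0.8 = 4.80, rate about 0.028 (simulated 0.023 to 0.036).

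**Step 3, power at 200 births per cell.** Fitting the model to the expected counts, categorical period, gives:

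| Event | LR statistic | LR p | Robust Wald p |
|---|---|---|---|
| Success (RR 1.125) | 2.018 | 0.155 | 0.00025 |
| Failure (RR 0.50) | 11.745 | 0.0006 | 0.00024 |

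For success, the signed root of the LR statistic is √2.018 = 1.42, and the robust Wald z is 3.66. Their ratio is 1.42/3.66 = 0.388.
- Robust Wald power: Φ(3.66 − 1.96) = Φ(1.70) ≈ 96%.
- LR power: Φ((1.42 − 1.96)/0.388) = Φ(−1.39) ≈ 8%.

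At 266 births both z values rise by √(266/200) = 1.153.
- Robust Wald: Φ(4.22 − 1.96) ≈ 99%.
- LR: Φ((1.64 − 1.96)/0.388) ≈ 20%.

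**Step 4, results on Table 2, categorical period.**

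| Births per cell | LR, success | Robust Wald, success | LR, failure | Robust Wald, failure |
|---|---|---|---|---|
| 200 | 8.2% | 95.5% | 93.9% | 95.6% |
| 250 | 16.9% | 98.4% | 97.6% | 98.4% |
| 266 | 20.3% | 98.8% | 98.3% | 98.8% |

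Independent simulations agree: success-coded LR power was 8-9% at 200 and 18-20% at 266, and failure-coded LR power was about 95% at 200. A model-based Wald test under success coding had 8.9% power at 200. With a linear time term the success-coded LR figures are 11%, 22% and 26%.

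**Step 5, sensitivity to layout.** The article limits collection to 12 months per site but does not fix which cells fall within it. In assumed layouts of 14 to 16 cells (2,800 to 4,256 births), success-coded LR power is 0.3-8%, against 65-94% for the robust Wald test.

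**Step 6, AIC.** Categorical periods use four more parameters than a linear trend (5 against 1), so AIC prefers them when the LR statistic exceeds 2 × 4 = 8. On the correct scale that means exceeding 8/0.2 = 40 for success at 80%, but 8/0.8 = 10 for failure at 20%. In simulation:
- period pattern in failure of 0/+5/0/−5/0/+5 points: linear chosen in 92% of success-coded datasets and 0% of failure-coded ones;
- a 5-point step: linear in 100% and 74%;
- success-coded, alternating effects on log failure risk: at ±0.1, linear in about 100%; at ±0.25, categorical in 24% (effect present) or 84% (no effect); at ±0.4, categorical in 100%;
- success-coded, a single 0.4 step: linear in 98-100%.

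After AIC selection, the robust Wald test had type I error of 5-9% and power of 84-98%.

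**The case against.** **The collapse needs two choices that the protocol does not fix.** This stands. A reader might infer that the planned primary test has almost no power, but the text ranks neither test, and a Wald test from the stated robust fit is sound. Nor is success firmly the modelled event. The outcome is worded as a success rate, but the same sentence dichotomises it without saying which level is the event, while the abstract, the outcome definition, the sample size scenarios and the tabulation plan all use failure. Under failure coding the power loss on Table 2 is one to two points, and the error is conservative.

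**The test sentence may be generic,** since the same strategy is carried to linear and multinomial models, where a likelihood-ratio test is legitimate. This helps only in part: the sentence sits under Main analysis and governs the primary model.

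**AIC.** A reader might infer that AIC nearly always picks the simplest trend. The simulations show that this depends on the size and shape of the trend, and the consequence for the robust Wald test is modest. The article also names AIC only as an example.

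**Other stronger readings.** A reader might expect the p-value to contradict a robust confidence interval reported beside it, but the section promises no interval. The 96-99% figures use all 20 cells and should not be read as what 12 months per site will deliver. Requiring categorical periods would be partly a matter of preference, since both forms are pre-specified.

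**Conclusion.** The point holds in limited form: the protocol states a rule that can give a wrong primary result. A likelihood-ratio test, or a Wald test with model-based variance, is not valid for the modified Poisson model.

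If success is the event, likelihood-ratio power on the full Table 2 layout is about 8-9% (200 per cell) to 18-20% (266), against about 96-99% for the robust Wald test, with type I error near 0. If failure is the event, power is about 95% and type I error about 3%. AIC has the same scaling fault, with an effect that depends on the trend.

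These figures assume the planning rates of 20% and 10%, equal cell sizes, unit and categorical period fixed effects, and all 20 cells. They depend on the period adjustment, which the protocol requires. Without it, likelihood-ratio power would be at least 98% in every layout examined.

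**What to change.** Make four changes to the Main analysis section:

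1. State that the intervention effect is tested with the Wald test using the robust (sandwich) variance, and that any confidence interval uses the same variance.
2. Delete the likelihood-ratio option for modified Poisson models. It can remain for models fitted with a correct likelihood.
3. State failure with the first instrument as the modelled event, in line with the Primary outcome measure section.
4. If time is chosen by a fit criterion, use QIC or a binomial likelihood instead of the Poisson AIC.

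The cost is a few sentences. No change to design, data collection or sample size is needed.
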